# Independent Housing and Support for non-homeless individuals with severe mental illness: randomised controlled trial vs. observational study – study protocol

**DOI:** 10.1186/s12888-020-02712-y

**Published:** 2020-06-19

**Keywords:** Residential rehabilitation, Supported housing, Non-homeless people, Serious mental illness, Randomised controlled trial, Observational study design, Non-inferiority

## Abstract

**Background:**

Social inclusion is essential for an adequate rehabilitation process for people with serious mental illness (SMI). Various supported housing settings aim to promote housing competencies and social inclusion in service users. Nevertheless, there is a strong preference in service users for independent living. We aim to evaluate the effectiveness and efficiency of Independent Housing and Support (IHS) compared to institutionalised residential care settings and other treatment as usual conditions (RCS/TAU) in two cities in Switzerland.

**Methods:**

This is a prospective multi-centre, four-arm, non-inferiority cohort study investigating the effectiveness and efficiency of IHS and RCS/TAU for people with SMI. Effectiveness will be measured by a standardised measure of social inclusion as primary outcome as well as by measures of functioning and well-being. Efficiency will be analysed on the basis of service usage and costs associated with the different housing settings. Participants will be consecutively recruited and subsequently enrolled between April 2019 and December 2020 and assessed at baseline and after six, twelve and after 24 months. At one study site, 56 participants will be randomly assigned to one of the conditions; the other study site will be conducted as an observational study investigating 112 admitted participants.

**Discussion:**

While the UN Convention of the Rights of People with Disabilities aims to promote the opportunity to choose one’s place of residence, the limited supply of alternative forms of housing does not guarantee genuine freedom of choice. Increased diversification and flexibility of housing support is essential. If IHS shows non-inferiority in terms of their effectiveness and efficiency, users should be allowed to choose their kind of housing support.

**Trial registration:**

ClinicalTrials.gov: NCT03815604, December 04, 2019.

## Background

Along with the deinstitutionalization which has taken place since the 1960s, psychiatric care has made a shift from inpatient care to community based services [1]. As a consequence, housing and housing rehabilitation of people with serious mental illness (SMI) and their social inclusion became major elements of mental health care. However, housing rehabilitation for people with SMI is a neglected research field, and its implementation is largely based on the knowledge from the 1980s/90s [2].

With the UN Convention on the Rights of Persons with Disabilities [3], a basis has been built for people with disabilities to achieve a range of services according to their choice. Article 19 in particular aims to enable people with SMI a) to “have the opportunity to choose their place of residence”, b) to “have access to a range of in-home, residential and other community support services” and c) that services and facilities are “available on an equal basis to persons with disabilities and are responsive to their needs” with the goal of social participation and inclusion. Unfortunately, the implementation of the article has not advanced greatly since its passing, and allocation is more often driven by availability than by users’ choice or needs [4].

The common approach in psychiatric rehabilitation in many countries relies on a linear continuum of residential services that aims to enable the person with SMI to eventually live independently. This continuum contains several settings of different amounts of support and restrictiveness. In each of these settings, users are to become stabilised and learn specific housing skills. Once the client’s level of functioning improves, he or she “graduates” to move to a more independent setting [1]. However, current state of research shows clearly that most people in question do not reach the goal of living independently and remain in institutionalised residential care settings [5–7].

In line with the UN Convention, there is another form of residential rehabilitation called the Supported Housing model [1]. The model aims to place a person without prior housing arrangements directly into accommodation in the community, even if the individual is in need of specialized psychiatric or psychosocial care. The accommodation is independent of therapy or care and is rented by the service user according to his or her choice. Unlimited support is provided by off-site professionals concerning all aspects related to keeping the accommodation and according to individual needs. The main goal is seen in the social inclusion of service users into real life networks.

The heterogeneous terminology and conceptualization of various existing housing models complicate a comparison of different residential support services. Several attempts at creating a taxonomy were undertaken [8–10]. However, there is currently no consistent and widely acknowledged taxonomy available, and same setting labels often have different conceptualisations. The supported housing approach is sometimes entitled “supported” or “supportive” housing, whilst in England it is often called “floating outreach” or “floating support services”, e.g. [4, 11]. Based on the UN Convention on the Rights for Persons with Disabilities [3] and on early conceptual work in the US by the National Association of the State Mental Health Program Directors cited in Hogan and Carling [12] the supported housing model in this study is entitled Independent Housing and Support (IHS). The institutionalised residential rehabilitation services following the linear continuum of residential support services are labelled as residential care services and other treatment as usual conditions (RCS/TAU).

From a service user’s perspective, the supported housing approach has several advantages compared to the linear continuum approach of residential rehabilitation. Firstly, users of the supported housing model live in their own accommodation and not just in a housing setting. Experiencing one’s place of residence as one’s home is associated with more autonomy, empowerment and personal recovery [13–15]. Secondly, users do not have to move following a change of their needs. Due to the fluctuating nature of mental disorders and the requirement for a stable environment to maintain health, there is a recommendation for offering unlimited length of stay [16]. Thirdly, support in gaining housing skills is related to real-world requirements and not just to the respective settings environment. As a consequence, the main goal of supported housing is social inclusion rather than being supported according to the state of disability.

A substantial number of supported housing programs are designed with a focus on homeless people. Most prominent are the *Housing First* approach [17] and the HUD-VASH program (*Department of Housing and Urban Development – Veterans Affairs Supportive Housing Program* [18]). These programmes were initially developed in the United States and Canada and aim to support housing stability or permanent accommodation without the requirement of prior abstinence or therapy. Housing First programmes for homeless people are outperforming RCS in in many outcomes, such as healthcare utilization, reduction of substance use or improvement of mental health [19, 20].

In contrast, evidence for residential rehabilitation approaches for non-homeless people is less clear [16, 19–22]. Unlike the supported housing models for the homeless, IHS for non-homeless people with SMI mainly focus on psychosocial outcome variables like reduction of rehospitalisation rates and improving social functioning [19]. On the one hand, comparative analysis showed inconsistent results and no significant differences in outcomes between IHS and RCS could be found [20]. On the other hand, studies focusing on non-homeless people vary greatly in their methodological quality and none of them were conducted as randomised controlled trials. Nevertheless, there are some promising results of IHS for people with SMI.

Several studies show people with SMI to be more socially excluded than comparison groups [23, 24]. Concerning independent housing, some studies suggest that these conditions are socially isolating and foster experienced loneliness compared to living in a group home [14, 25], while the latter is assumed to promote a sense of community [26]. In contrast to this notion, other researchers believe there is a risk in re-establishing social relationships which rely on interactions with RCS-staff to overcome loneliness [14]. Another study highlights the importance of having a choice in when to socialize and when to be alone, and revaluate the “alone time” as an important aspect of the recovery process and as a specific advantage of IHS [27]. Furthermore, there are studies showing service users of IHS to be more socially included [13] and engaged in community [28].

There are only a small number of studies investigating the costs of residential rehabilitation programmes, especially with regard to non-homeless people. In general, varying welfare state conditions between countries make it difficult to compare costs of residential support programmes. Nevertheless, researchers report significant differences in costs in favour of IHS [29] as well as better cost-effectiveness [30, 31].

Furthermore, there is a strong preference of service users for independent living. According to a recent meta-analysis, 84% of service users expressed the desire to live independently when asked about their housing preferences [32]. This finding replicated previous results from the 1990s [33]. However, there is a difference in the preferred support service between service users and their care givers and families. While service users tend to prefer more independent permanent accommodation, staff and family members usually prefer the person to reside in more supported settings [34, 35]. However, having an opportunity to choose one’s place of residence is associated with greater subjective quality of life and adaptation to community living [36] and largely contributed to mental health recovery and wellbeing [27].

### Methodological considerations

Up to now, no randomised controlled trial (RCT) has been conducted with non-homeless populations to evaluate the efficacy of IHS. The aforementioned strong preferences minimise the likelihood of the realisation of RCTs investigating residential rehabilitation approaches for people with SMI. One factor is that the living situation of non-homeless people is usually already determined and the feasibility of a random allocation to a particular housing condition is, thus, questionable. Another factor is that patient preferences are known to have a tremendous effect on non-enrolment into an RCT or a higher risk of dropouts in the non-preferred condition [37–39]. Furthermore, a recent feasibility study failed in supporting large-scale randomised trials due to a high level of “gate keeping” by staff and strong preferences of service users for one of the two types of supported accommodation [4].

RCTs are widely acknowledged to be the “gold standard” of comparative research. However, alternatives are needed where RCTs are not feasible. It is now widely acknowledged that observational study designs (OSD) may provide important results that seem to be comparable with results of randomised controlled studies [40–42]. Moreover, a Cochrane review of 14 reviews covering 1583 studies did not find any significant differences in effect estimates of general healthcare outcomes between randomised controlled and observational studies [43]. While there is somewhat the worry that OSD generate overestimated effectivity due to self-selected referral resulting in a selection bias, other authors underline the possibility of underestimating intervention effects due to the naturalistic and therefore more heterogeneous “real-life” settings, e.g., [44]. Generally, OSD are able to provide external validity rather than internal validity.

## Methods

### Aims of the study

Based on these findings, we aim to investigate both 1) a care-related and 2) a methodological goal with the current multi-centre study to answer the following research questions:
What are the effectiveness and efficiency of IHS compared to RCS/TAU for non-homeless persons with severe mental illness after 6, 12, and 24 months?Do the RCT and the OSD yield similar results?

The primary objective is to evaluate the effectiveness and efficiency of IHS and to directly compare it to traditional RCS/TAU for non-homeless people with severe mental illness. Effectiveness will be determined by social inclusion, proposed as a key outcome for individuals living with mental disorders and, in terms of research, a global priority measure [45]. Efficiency will be analysed based on the costs associated with the service utilization of the different housing settings. As the political goal is seen in allowing a freedom of choice in where to live and which support services to utilise [3] and because the differences in outcomes of previous studies between IHS and RCS for non-homeless populations were only small or inexistent [16, 19–22], we utilise a non-inferiority hypothesis in our study. We hypothesize that IHS yields no poorer social inclusion outcomes than traditional RCS/TAU.

One study centre is going to conduct an OSD with propensity score matching methods and the other center plans to conduct an RCT while learning from the results of the recently failed feasibility trial of IHS [4]. Thus, to our knowledge, the present study will include the first RCT investigating housing conditions for non-homeless people with SMI. The secondary objective of this study is to directly compare the outcomes of the RCT with the OSD. Here, we utilise the hypothesis that the OSD will provide similar results to the RCT. If the hypothesis is confirmed, observational studies investigating residential rehabilitation programmes for the non-homeless population could be considered as equivalent to the RCTs so far solely conducted with respect to homeless people.

In addition, we will conduct secondary analyses to investigate the moderation, mediation and procedural factors in IHS and RCS/TAU that influence outcomes.

### Study design

The present field-study is a prospective, multi-centre, four-arm, parallel-groups, cohort, non-inferiority open trial comparing Independent Housing and Support (IHS) with traditional residential care settings and other treatment as usual conditions (RCS/TAU) for non-homeless people with SMI in two cities in Switzerland (Bern and Zurich). To conduct the RCT, a specific time window is used in Zurich where IHS is going to be newly introduced. Access to IHS will be limited for study participants during recruitment to the study, so the realisation of an RCT will be possible due to a scarcity of IHS settings. Because IHS is already well-established in Bern, a comparative observational study with propensity score matching will be conducted there. Both, the RCT part and the OSD part of this study aim to prove the non-inferiority of IHS compared to RCS/TAU.

### Sample size

The appropriate sample size is determined by the non-inferiority approach and was calculated for the primary outcome measure ‘Social Functioning Scale’ [46, 47]. This scale has been used in a subsample of a randomised Housing First trial, from where the necessary data has been taken [48]. For calculating the appropriate sample size of the RCT study site, the application ‘Power and Sample Size’ [49] was used applying the following parameters: Power: 0.9; significance level: 0.025; non-inferiority margin: 15; difference between treatments (group means): 111.2–106.7; standard deviation: 12; and allocation ratio: 1:1. This procedure yielded a sample size of 28 people to be included in each arm.

The OSD sample size is based on the calculation for the RCT. Thus, 28 participants will be included in the treatment arm. For propensity scoring, the many-to-one matching method was chosen. Here, it is recommended to have a 2–3 times larger control group to facilitate matching [50, 51]. Accordingly, 56 to 84 participants will be included in the control group.

### Eligibility criteria

Eligible participants are composed of the target population of the investigated residential rehabilitation settings IHS and RCS/TAU. All included study participants have a primary mental disorder according to the International Classification of Diseases, 10th edition (ICD-10), are aged between 18 and 65 years, are able to communicate in the German language, to give informed consent, and to take their medication if indicated. They are also able to handle out of pocket expenses or have an established assistance of a custodian/guardian if indicated. The presence of any of the following criteria will lead to the exclusion of a potential participant: severe learning disabilities, intoxication, delirium, dementia, lack of capacity, an indication for hospital treatment due to acute symptomatology at admission and acute risk to self-harm or harm to others.

### Participant recruitment

Participants will be recruited between April 2019 and December 2020 within the conventional pathways to gain access to psychiatric residential rehabilitation. At the RCT study site, participants interested in IHS will be consecutively recruited by study collaborators. After agreeing to participate, a study collaborator will explain the purpose and procedures of the study. If the participant gives informed consent, she or he will be subjected to randomisation. For each participant, the result of randomisation is enclosed in an envelope based on a randomisation sheet, which has been calculated before study start for more than 56 consecutive cases. For this calculation, the statistical software R has been used with the procedure for block-randomisation described at [52]. The randomization sheet is saved in a formal study folder only accessible to researchers not involved in the allocation procedure so that no spontaneous modifications can be made during the study enrolment. Subsequently, the treatment condition to which they were randomly assigned will be arranged and the participant is then enrolled. For each measurement point at the RCT study site, participants will receive ten Swiss Francs. The goal of this financial compensation is to minimise potential dropouts in the control group, which have to be assumed due to the strong preference for IHS [32, 33] and the associated difficulties in the enrolment of an RCT [37, 38], especially in the field of supported housing [4].

At the OSD study site, participants will be consecutively recruited by residential rehabilitation staff or by social workers at the mental health hospital they are discharged from. After being admitted to the respective treatment condition, a study collaborator will ask them to give informed consent. Consenting participants will be subsequently enrolled into the observational study.

At both study sites, service users are considered to be intent-to-treat (ITT) after using their respective residential rehabilitation service for at least one month. Participants not considered to be ITT due to withdrawal before one month will be excluded from the study. If participants leave their residential rehabilitation setting after using it for at least one month, assessments with participants will continue in order to investigate the further progress of residential service users. Each dropout occurring during the recruitment phase will be replaced by a new subject in order to ensure an adequate number of participants in in each condition according to the power analysis. In case of dropout, all corresponding data on the contact sheet will be deleted and the person will never be contacted again. However, study data assessed before will be retained. Recruitment is complete when the intended number of participants is reached, after 21 months’ recruitment period at the latest. For the methodological objective, every participant at both study sites will be asked to consent for further use of data in encrypted form.

All assessed data will be entered in REDCap [53]. Participants will be coded and no personal data will be disclosed. The assessors of each study site will store personal data in password-protected files in order to contact them for conducting the assessments on a drive of the university.

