### Primary objective: care-related goal

For analysing the primary outcome variable social inclusion we will check for non-inferiority both in per-protocol and in imputed ITT samples to assess the security of inference of non-inferiority as recommended in the CONSORT guidelines for non-inferiority trials [72, 73].

Primary analysis will compare primary and secondary outcomes between IHS and RCS/TAU after 6, 12 and 24 months separately for both study sites. A repeated measure approach will be used where indicated. Non-inferiority of IHS compared to RCS/TAU will be accepted based on a 2.5% significance level if the lower bound of the 97.5% CI of M_IHS_-M_RCT/TAU_ is > δ = − 15, and vice versa, non-inferiority of IHS compared to RCS/TAU cannot be accepted if the lower bound of the 97.5% CI of M_IHS_-M_RCT/TAU_ is ≤ δ = − 15. This non-inferiority margin corresponds to one standard deviation of 15 scale scores (*m* = 100; *SD* = 15) on the primary outcome variable SFS [46, 47] and was chosen based on the clinical judgment of experts as no RCT investigating the SFS as outcome measure in a comparable sample was available [81]. In addition, assay sensitivity will be analysed by investigating pre-post differences in a first step. Assay sensitivity will be assumed, if there is a statistically and clinically significant pre-post increase in the SFS total scale score [82].

All other outcome measures will also be tested on their non-inferiority using the definition of margin δ as one standard deviation of the respective scale. Analyses will be extended to superiority testing in case of confirmed non-inferiority, and to interaction terms to explore mechanisms of treatment effects.

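### At the RCT site the ITT set is conditioned on one month of service use after open randomisation, so no set of all randomised participants is analysed; the resulting bias has no known direction

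*Protocol article*

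**What the plan says.** Under Participant recruitment, the rule for both sites is that "service users are considered to be intent-to-treat (ITT) after using their respective residential rehabilitation service for at least one month". The consequence for earlier leavers follows: "Participants not considered to be ITT due to withdrawal before one month will be excluded from the study". Later leavers are treated differently: "If participants leave their residential rehabilitation setting after using it for at least one month, assessments with participants will continue".

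At the RCT site the order is consent, randomisation, then housing: "Subsequently, the treatment condition to which they were randomly assigned will be arranged and the participant is then enrolled". The Study design section describes an open trial, and Limitations says that blinding is not possible.

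On dropouts, the same section says: "Each dropout occurring during the recruitment phase will be replaced by a new subject in order to ensure an adequate number of participants". Contact details of a dropout are deleted and no further contact is made. On what was collected before, it says: "However, study data assessed before will be retained".

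The section on the primary objective (care-related goal) says of the primary outcome that "we will check for non-inferiority both in per-protocol and in imputed ITT samples", and cites the CONSORT guidance for non-inferiority trials as the reason.

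The article also says where it expects losses. The payment per assessment at the RCT site is meant to "minimise potential dropouts in the control group, which have to be assumed due to the strong preference for IHS". The Challenges section names attrition bias as the main risk of the RCT, and Data analyses assumes that data lost through dropout are missing not at random.

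**The concern.** Intention to treat means that the arms compared are the arms randomised. Here a randomised person counts only after a month of using the assigned service, and anyone who withdraws earlier leaves the study. That event comes after allocation, is known to participant and staff, and can depend on the arm. The groups that remain are then no longer protected by randomisation.

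The rule also undermines the plan's own safeguard. Testing non-inferiority in two populations helps because one keeps everyone randomised and the other keeps those treated as planned. If both omit the early leavers, agreement between them says nothing about the effect of that omission. Imputation cannot help, because it fills gaps only for people who are in the set. Nor can the loss be repaired later: the first follow-up is at 6 months, so someone excluded in the first month has at most baseline data.

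**Working it through.** **Inputs from the article.** Sample size section: power 0.9, significance level 0.025, margin 15, group means 111.2 and 106.7, SD 12, 1:1 allocation, 28 per arm. Primary objective section: non-inferiority is accepted if the lower confidence limit for IHS minus RCS/TAU lies above -15, at a 2.5% level.

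**The plan's own figure.** Difference = 111.2 - 106.7 = 4.5. Taking IHS as worse by 4.5, the distance to the margin is 15 - 4.5 = 10.5.

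n per arm = 2 x [12 x (1.960 + 1.282) / 10.5]^2 = 27.45, rounded up to 28.

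The stated size reproduces. With a noncentral t (54 degrees of freedom), power at 28 per arm is 0.895. The sample size is not the fault.

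**Bias from the exclusion.** Let p be the share of an arm excluded in the first month, and g the mean SFS of the excluded minus that of the retained. The mean of all randomised in an arm is the retained mean plus p x g. The retained comparison therefore differs from the all-randomised comparison (IHS minus RCS/TAU) by

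shift = -p(IHS) x g(IHS) + p(RCS/TAU) x g(RCS/TAU).

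The article gives neither p nor g. As an assumption, take g as one planning SD, 12 points:

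- 20% of IHS excluded, leavers 12 points worse, none excluded in control: -0.2 x (-12) = +2.4.
- 20% of control excluded, leavers 12 points worse, none in IHS: 0.2 x (-12) = -2.4.
- 20% of control excluded, leavers 12 points better, none in IHS: 0.2 x 12 = +2.4.
- 10% of each arm excluded, leavers 12 points worse in both: +1.2 - 1.2 = 0.

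**Effect on the decision.** Standard error = 12 x sqrt(2/28) = 3.207. The noncentrality is shift / 3.207 at a true difference of -15, and (10.5 + shift) / 3.207 at a true difference of -4.5. This assumes 28 analysed per arm (leavers replaced) and an SD of 12 among those retained.

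| Shift (points) | One arm affected, for example | One-sided error at -15 | Power at -4.5 |
|---|---|---|---|
| +3.0 | 25% x 12 | 14.9% | 0.985 |
| +2.4 | 20% x 12 | 11.0% | 0.977 |
| +1.2 | 10% x 12 or 20% x 6 | 5.6% | 0.948 |
| 0 | equal p and g in both arms | 2.5% | 0.895 |
| -1.2 | 10% x 12 or 20% x 6 | 1.0% | 0.813 |
| -2.4 | 20% x 12 | 0.35% | 0.699 |
| -3.0 | 25% x 12 | 0.2% | 0.632 |

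If losses fall mainly in the control arm, the sign depends on whether control leavers function worse or better than those who stay.

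**The case against.** A reader might infer four stronger things. The article supports none of them.

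*The bias favours non-inferiority.* No section says whether early leavers score higher or lower on the SFS. An expectation of control dropout, and of data missing not at random, gives no sign. The usual stories are also weakened by the Interventions section. The IHS coach helps with finding a flat, so someone still searching may already be using the service. Unsupervised living is listed within RCS/TAU, so living alone is not in itself leaving the control condition.

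*The two-population check is worthless.* It is weakened, not void. Those who leave after the first month are still assessed and stay in the ITT set, whereas a per-protocol set would ordinarily drop them.

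*Replacement by itself biases the comparison.* It applies only to dropouts during recruitment, and data already collected are kept. The article does not say that a replaced person who passed one month leaves the ITT set. The randomisation list covers more than 56 cases, so taking the next number fits the current text. Combined with the exclusion, however, replacement restores the count and makes the loss less visible.

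*The same fault applies at the observational site.* Nobody is randomised there and consent follows admission. The one-month rule is a cohort definition; it can cause selection but breaks no randomised comparison.

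It is also fair to say that the article expects study dropout in the control arm, not specifically withdrawal in the first month. An arm difference in the first month is plausible but not stated. Some early leavers will have withdrawn consent and cannot be followed under any rule.

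What stands is the definition. The article fixes it, so it is not a detail left to an unseen analysis plan.

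**Conclusion.** The concern holds for the RCT site in this form: the set called ITT is conditioned on a month of use after open randomisation, earlier withdrawals are removed, and the article describes no analysis of all randomised participants. This rests on the text alone.

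That the result may be biased rests on the plan's own expectation of control-arm dropout and of outcome-related missingness. The size rests on assumed rates and gaps. With 20% of one arm excluded and a 12-point gap, the one-sided error at the margin becomes about 11% or about 0.35%, depending on sign, and in the second case power falls from about 0.90 to 0.70. With equal rates and gaps in both arms there is no shift. The direction is unknown, but that does not make the rule safe: the analysis as defined cannot rule out an inflated chance of falsely declaring non-inferiority. The rule should be corrected before the RCT is analysed.

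**What to change.** For the RCT:

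1. Define ITT as every randomised participant, analysed in the assigned arm, whether or not the housing was taken up.
2. Separate leaving the housing from withdrawing consent. Seek the 6-, 12- and 24-month assessments from early leavers who have not withdrawn consent. Include the others through imputation, with sensitivity analyses that allow for data missing not at random.
3. Call the one-month set modified ITT or per-protocol.
4. If dropouts are replaced, use the next number on the existing list, whichever arm it gives, and keep the replaced person in ITT.

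For the observational site, describe the one-month rule as the cohort definition and do not call the result ITT.

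The cost is a change of wording, a few extra follow-up contacts, more missing data and possibly somewhat lower precision. If leavers could be neither followed nor replaced, assumed losses of 10%, 20% and 30% leave 25, 22 and 19 per arm. Power is then about 0.87, 0.83 and 0.77 by the normal approximation, which gives about 0.91 at 28 per arm (10.5 / 3.207 - 1.960 = 1.314). Holding 28 with data would need 28 / (1 - loss) = 32, 35 or 40 per arm. The current plan already replaces dropouts during recruitment, so continuing down the list asks for little beyond what is already foreseen.
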